### **Adverse Event Reporting:**

In case of a serious adverse event, please report to the Principal Investigator ([name] [name]) immediately and the Principal Investigator will be required to report it to the PolyU IRB within 48 hours upon the receipt of your report.

SAE is any adverse event that:

- Results in death
- Is life threatening, or places the participant at immediate risk of death from the event as it occurred
- Requires or prolongs hospitalization
- Causes persistent or significant disability or incapacity
- Results in congenital anomalies or birth defects
- Is another condition which investigators judge to represent significant hazards

(Reference: NIA Adverse Event and Serious Adverse Event Guideline)

### **Statistical Analysis Plan:**

Assessment will be administered by a research postgraduate student with speech therapy background or trained speech therapy students who are blinded to the assignment of treatment condition. Scoring will be done by the research postgraduate student. Data analyses will be carried out by PI and Co-Is. Treatment and generalization probes will be scored by the Naming and Oral Reading for Language in Aphasia 6-point scale (NORLA-6) with some adaptations. NORLA-6 has been validated (Pitts et al., 2018) and adopted in a number of script training studies (e.g., Cherney et al., 2014; 2019). (R2) Adaptations in the current study concern the accuracy judgment of responses that semantically acceptable production will also be considered accurate during scoring. The time for script production will also be calculated. For secondary outcomes, PWA's performance on various cognitive tasks and CANELT will be transformed into z-scores. A principal component analysis will be carried out to group tests that share similar cognitive components. Linear mixed effect (LME) models will be used to investigate the research questions with timepoint and experimental conditions as fixed variables and different primary/secondary outcomes as predicted variables. Any significant results will be followed by post-hoc comparisons. Variables that may interfere with the outcomes such as age, aphasia severity, and education, will be included and controlled in the model.

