## **Study Design**

A prospective, three-armed, open-label, assessor-blinded RCT will be conducted over a period of 20 weeks, based on a treatment protocol developed by the project team (Wong & Li, submitted). Protocol design and data reporting are aligned with the Consolidated Standards of Reporting Trials Statement (CONSORT) for nonpharmacologic trials (Boutron et al., 2017).

Trial Registration Data Set has been registered in ClinicalTrials.gov (NCT06722092).

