### **Secondary Objectives**

Secondary outcome on nonverbal cognition is comprised of a test battery measuring EF, short-term/working memory, and attention used in previous studies of PI that investigated the relation between nonverbal cognition and multi-level language processing (Wong & Law, 2022a) and their changes as a result of functional communication therapy (Wong & Law, 2022b). Attention is assessed via sub-tests 1 (map search) and 3 (elevator counting) of the Test of Everyday Attention (Robertson et al., 1994). The former aims to tap sustained and selective visual attention via identifying the target symbol in a map while the latter assesses auditory selective attention via counting the number of target tones in the presence of distractors with different tones. Verbal short-term and working memory will be examined via digit span forward and backward tasks from the Wechsler Adult Intelligent Scale – 4th edition (2008), respectively. EF will be evaluated via the Test of Nonverbal Intelligence-third edition (TONI-3; Brown et al., 1997), and the Wisconsin Card Sorting Test (WCST; Grant & Berg, 1993). TONI-3 is a norm-referenced test that uses abstract figures to evaluate abstract reasoning and problem-solving. WCST assesses cognitive flexibility and reasoning via matching cards with respect to color, quantity, and shape upon different rules and feedback given.

In accordance with the Research Outcome Measurement in Aphasia (ROMA; Wallace et al., 2018), the aphasia quotient of CAB, and CANELT (Wong et al., 2023), a standardized 6 measure adapted from the Amsterdam-Nijmegen Everyday Language Test (ANELT; Blomert et al., 1994), will be included as secondary outcomes in language and communication, respectively. CAB is a standardized aphasia test for measuring aphasia severity. CANELT assesses verbal communication effectiveness in conversation via 20 culturally appropriate scenarios. PWA's self-reported outcome on communication and quality of life will be examined via the Cantonese version of the 20-item

Communication Outcome after Stroke (Can-COAST) Scale (Kwok & Wong, 2023) translated from its original English version (COAST; Long et al., 2008). All assessment tasks and their sources of normative data (if applicable) are summarized in Table 1.

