### **Privacy and confidentiality:**

1. No subject identifying information, other than recorded audio files of the subject's voice, will be recorded in any location other than the subject's signed consent form.
2. Code numbers will be assigned and used on all materials. Signed Informed Consent forms will be kept in a separate file from all coded materials.
3. Only the investigators and the team members of the current project will be permitted to access

the audio recordings, data, and consent forms. Furthermore, access to the data is password protected. Responsible members of The Hong Kong Polytechnic University may be given access for monitoring and/or audit of the research.

4. If the results of this study are published or presented in public, only transcripts with code numbers will be used.
5. At the end of three years after the completion of the study, all personal identifiers will be removed. However, anonymized data (including audio recordings) will be kept indefinitely for data sharing.

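### One role may both administer and score the judged outcomes in an open-label trial, so the declared assessor blinding is weakly protected

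*Protocol*

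**What the plan says.** The Study Design section describes "A prospective, three-armed, open-label, assessor-blinded RCT will be conducted over a period of 20 weeks". Participants therefore know whether they had a headset, a screen or nothing, and the assessor is meant not to know.

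The Statistical Analysis Plan section assigns the roles. On testing: "Assessment will be administered by a research postgraduate student with speech therapy background or trained speech therapy students who are blinded" to the assigned condition. On scoring: "Scoring will be done by the research postgraduate student". The probes are scored on an adapted NORLA-6 scale under which "semantically acceptable production will also be considered accurate during scoring". No second rater is named.

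The Secondary Objectives section adds another outcome that rests on spoken interaction: "CANELT assesses verbal communication effectiveness in conversation via 20 culturally appropriate scenarios".

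The Primary Objective section has accuracy and time on the trained scripts captured by the training program. The Privacy and confidentiality section shows that voice recordings are kept, and says "Code numbers will be assigned and used on all materials".

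**The concern.** In an open-label trial, assessor blinding is the main safeguard for outcomes that a person must judge. Here it can be lost in an ordinary way. A participant who knows the arm talks to the tester, mentions the headset or the lack of any training, and the tester later decides whether that participant's productions count as acceptable. The protocol allows tester and scorer to be the same person and sets no barrier between the two tasks.

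At stake is judged accuracy on the treatment and generalization probes, and CANELT among the secondary outcomes. If a scorer who has learned the arm is more lenient towards trained participants, the error favours the hypothesis. A larger sample would not reduce it, and the planned mixed model could not separate it from a treatment effect.

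**Working it through.** The protocol states no figure on this point, so the check is mainly a reading of its sections side by side.

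**1. Can tester and scorer be the same person?** Yes. The testing sentence begins "Assessment will be administered by a research postgraduate student with speech therapy background or" and names the students as the alternative. The scoring sentence uses the definite article for the postgraduate student, which points back to the same role. The section on sample size and eligibility also lets a research postgraduate student or a research assistant do the screening, so contact may begin earlier.

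**2. Is the scorer declared blinded?** At trial level, yes: Study Design says the assessor is blinded. In the role description the clause "trained speech therapy students who are blinded to the assignment of treatment condition" may cover both kinds of tester or only the students. The scoring sentence itself says nothing about blinding.

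**3. Does scoring need judgement?** For probe accuracy, yes, because semantic acceptability must be decided. Production time, the other part of the probe outcome, depends less on judgement.

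**4. Which comparisons are exposed?**
- *Knowledge of the visit alone.* If the scorer adds the same amount *b* at a given visit in every arm, the contrast between arms is (effect + *b*) − *b* = effect. Only change over time within an arm is biased.
- *Leniency towards anyone treated.* VR versus non-VR gives (effect + *b*) − *b* = effect. Treated versus no treatment gives effect + *b*.
- *VR versus non-VR.* This contrast is biased only if the scorer knows which of the two treatments was given and scores them differently.

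**5. Scale, as an illustration only.** The shift *b* is assumed; no document supplies it. With 105 participants in three equal arms, each arm has 105/3 = 35, and after 15% attrition 35 × 0.85 = 29.75, about 30. For a simple two-sided z-test of two arms at 5%, with outcomes in SD units, SE = √(2/n), and

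type I error = 1 − Φ(1.96 − b/SE) + Φ(−1.96 − b/SE).

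At n = 30, SE = √(2/30) = 0.258. For b = 0.2, b/SE = 0.775, and the two tails give about 0.118 + 0.003 = 0.121.

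| Assumed shift between arms (SD) | n = 30 per arm | n = 35 per arm |
|---|---|---|
| 0 | 5.0% | 5.0% |
| 0.1 | 6.7% | 7.0% |
| 0.2 | 12.1% | 13.3% |
| 0.3 | 21.3% | 24.1% |

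The table shows how sensitive a comparison with no treatment would be if such a shift existed. It is not evidence that one will occur, and the test is simpler than the planned mixed model.

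**6. Is there material for masked scoring?** In part. Program capture is described for the trained scripts, and audio files are kept. The code numbers appear under privacy; nothing says they hide the visit. It is not stated that CANELT is recorded, or how the generalization probes are captured.

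**The case against.** The strongest reply is that the protocol declares blinding in two places and contradicts itself in neither. Bias related to arm needs that blinding to fail, through disclosure or guessing, or needs the blinding clause not to reach the postgraduate student. Scoring order and file handling may also sit in a manual that is not shown. This stands as a limit on the claim. It does not remove the point, because the protocol itself assigns both tasks to one role.

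A reader might infer several stronger things that the documents do not support:

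- That the scorer works face to face and knows the visit. Neither is stated. Both would follow if the scorer also ran the session, but not if a student ran it and the scorer used a coded record.
- That knowing the visit biases the trial's comparisons. Alone, it cancels between arms.
- That the title question, VR against non-VR, is compromised. Equal leniency towards both treated arms cancels there.
- That the bias is a known share of the planned effect. The sample-size text says only that the effect is medium, without naming the measure, and no document gives a leniency. Such a share would divide one assumption by another.
- That coded recordings were set up for masked scoring. The codes are described as a privacy measure.

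**Conclusion.** The point holds in a limited form. The protocol permits one role to test participants who know their arm and then to score outcomes that require judgement. The declared blinding is therefore weakly protected; it is not shown to be broken. The exposed outcomes are probe accuracy and, as far as its scoring needs a rater's judgement, CANELT. The exposed comparisons are mainly treated versus no treatment. The size of any bias cannot be derived from the documents, and the table above is conditional on an assumed shift. The conclusion assumes that disclosure during testing is possible, which is plausible in an open-label trial of spoken communication but not documented. No figure in the protocol changes. The change is best made before assessments begin, because a live score given by someone who has learned the arm cannot later be made independent, although recorded probes could be rescored.

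**What to change.** In the Statistical Analysis Plan section of the protocol, state that:

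1. the person who scores is blinded to condition, so that the clause clearly covers the postgraduate student;
2. accuracy on the treatment and generalization probes is scored from the program's audio recordings, under code numbers that hide arm and visit, in an order randomised across participants and visits (first confirming that the generalization probes are recorded in the same way);
3. where existing staffing allows, a named assessor who did not administer that participant's assessment does the scoring;
4. the same applies to CANELT if it is audio-recorded.

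Hiding the visit protects statements about change within an arm and removes the cue that leniency after treatment would need. Moving only the visits after randomisation to the students would not be enough: the postgraduate student could still meet participants at screening or baseline, and the protocol does not say whether randomisation precedes or follows the two baselines. Student capacity is not stated either, hence the condition in item 3.

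The cost is modest. Scoring in batches finishes later than scoring visit by visit, and recordings must be relabelled so that the code does not reveal the visit. If CANELT is not currently recorded, item 4 would not apply unless recording were added.

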### **Informed Consent Process:**

Written informed consent will be sought from the participants with the presence of their caregivers.

### **Privacy and confidentiality:**

1. No subject identifying information, other than recorded audio files of the subject's voice, will be recorded in any location other than the subject's signed consent form.
2. Code numbers will be assigned and used on all materials. Signed Informed Consent forms will be kept in a separate file from all coded materials.
3. Only the investigators and the team members of the current project will be permitted to access

the audio recordings, data, and consent forms. Furthermore, access to the data is password protected. Responsible members of The Hong Kong Polytechnic University may be given access for monitoring and/or audit of the research.

4. If the results of this study are published or presented in public, only transcripts with code numbers will be used.
5. At the end of three years after the completion of the study, all personal identifiers will be removed. However, anonymized data (including audio recordings) will be kept indefinitely for data sharing.

**Risk/Benefit:**

Risk to participants: The procedure has no known risks. However, it is possible that frustration or fatigue may be experienced by some subjects occasionally. Cyber-motion sickness may be experienced during VR-based training. You will have at least a 5-10-minute break every half-hour in each assessment/treatment session. You may take breaks more frequently if you wish. A session may be terminated at any point if you feel fatigued and unable to carry on.

Potential benefits: The research project will provide valuable information that will have important implications for assessment procedures, treatment design and monitoring of therapy progress in individuals with aphasia. Participants will have a better understanding on their performance on communication, language, and cognitive functions through assessment in the study period. Their communication/language/cognitive functions may benefit from training.

**Study Timeline:**

Stage 1, screening, enrollment: 1-26th months

Stage 2, data collection: 4-32nd months

Stage 3, data extraction and data analysis: 6-33rd months

Stage 4, data wrap up and report writing: 33-36th months

**Data Safety Monitoring:**

The PI will be responsible for data safety monitoring and reporting of any incompliance with the protocol/ delay in study schedule.

**Conflict of Interest:**

The applicants have no conflict of interest to declare.
